### **Main analysis**

The main analysis relates to exploratory analysis of acceptability (% eligible who accept the offer of secondary distribution of kits to household or other close contacts) and contact acceptability (% contacts who self-test), safety (self-report of any social harms experience by the index patient), numbers of kits distributed, numbers of contacts accepting kits, number of contacts testing at least once, number of contacts with positive immediate or day 5 results, and number of contacts diagnosed within 5 days of symptom onset including asymptomatic contacts.

Qualitative data analysis will be captured by semi-structured interview during which index patients will also be asked about any perceived benefits and regrets, and their willingness to recommend secondary distribution to others testing positive for COVID-19.

### **Ethical considerations for the secondary distribution model**

Eligible index participants will be given detailed information about the study and will be invited to participate (NC06A). Written informed consent will be obtained before study procedures commences. Written informed consent also explicitly covers the potential for subsampling for the

process evaluation explaining that clients may be selected to be asked some additional questions about their experiences of the testing which means that the interviews could take up to 1hour.

Study information flyers will be distributed by the index patient to their contacts as part of the consent waiver. Consent requirements for each research activity.) Social harms will be expressly solicited via telephone call. No under 18s will be recruited for secondary contacts.

In addition, written informed consent will be obtained from index participants subsampled to take part in the patient cost exercise (NC09) at the point of diagnosis. If participants are illiterate, participant information sheets will be read to participants and thumbprint consent, alongside witness signature will be taken.

Written informed consent will also be obtained from the study providers for the 2 qualitative interviews (NC03).

## 5.2. Study place

12 health facilities shown below will be allocated for the non-randomized study:

| Facility | Programmatic COVID-19 Intervention (PCI) arm | Standard Of Care (SOC) arm |
|----------|----------------------------------------------|----------------------------|
|          | Bangwe Health Center                         | Chilomoni Health Center    |
|          | Chileka Health Center                        | Mpemba Health Center       |
|          | Dziwe Health Center                          | Lirangwe Health Center     |
|          | Mdeka Health Center                          | South Lunzu Health Center  |
|          | Chichiri Health Center                       | Limbe Health Center        |
|          | Ndirande Health Center                       | Zingwangwa Health Center   |

The 12 health facilities in Blantyre used for the health care worker use case above will also be selected for implementation and evaluation of the OPD use case.

Criteria for selecting a congregate setting in Blantyre for implementation of screening will be:

4. A working relationship must exist between the potential congregate setting and the district response team.
5. Must be one of the two below:
  - a. a university
  - b. a workplace
6. A gatekeeper must provide consent at institutional level for the implementation of screening.

### **5.3. Study population**

All HCWs (including administrators, maintenance staff, support staff, and clinicians) working in the targeted 12 health facilities of Blantyre District will be offered the opportunity to participate in the non-randomized controlled study.

#### **Inclusion criteria for healthcare workers**

Healthcare workers shall be eligible to participate if they are:

4. Aged 18 years and above
5. All health workers employed by the above facilities, including nurses, doctors, clinic assistants, health surveillance assistants, clinical officers, community health workers and lay counsellors, administrators and support staff with direct patient contact such as receptionists and porters.
6. Willing and able to give written informed consent

#### **Exclusion criteria for healthcare workers**

A healthcare worker shall be ineligible to participate if they:

3. Have tested positive for COVID-19 and are still within the isolation period
4. Have any medical contraindication to anterior nasal swab (e.g. bleeding disorders, recent facial trauma)

#### **Inclusion criteria for people in populated settings**

Residents of heavily populated environments shall be eligible to participate if they are:

5. Aged 18 years and above
6. Students/employees or residents of the institution or community where an outbreak is being investigated
7. Well enough to complete study activities
8. Willing and able to provide informed consent (written/thumbprint/verbal)

#### **Exclusion criteria for people in populated settings**

Residents of heavily populated environments shall be ineligible to participate if they:

4. Have tested positive for COVID-19 and are still within the isolation period
5. Have a medical contraindication to nasal swabs (e.g. bleeding disorders, recent facial trauma).
6. Are unable to provide informed consent

#### **Inclusion criteria for Outpatient Department attendees**

OPD attendees will be eligible to participate if they are:

1. Willing and able to provide written informed consent
2. Feeling well enough to comfortably conduct the study activities, as determined by participant reports and assessment by study staff.

**Exclusion criteria for Outpatient Department attendees**

OPD attendees will be ineligible to participate if they:

1. Have tested positive for COVID-19 and are still within the isolation period
2. Have any medical contraindication to anterior nasal swab (e.g. bleeding disorders, recent facial trauma)
3. Are unable to provide informed consent

For contact tracing component:

**Inclusion criteria for index case patients**

Index case patients shall be eligible for inclusion if they are:

5. Tested positive for COVID-19
6. Have at least one adult close contact at their place of residence
7. Do not feel at risk of physical harm, loss of employment or loss of housing from participating
8. Feeling well enough to comfortably conduct the study activities, as determined by participant reports and assessment by study staff.

**Exclusion Criteria for index case patients**

Index case patients shall be ineligible for participation if they are

1. Are unable or unwilling to provide informed consent
2. Not traceable or able to be interviewed by telephone

**Exclusion criteria for contacts**

Contacts shall be ineligible for participation if they are

1. Are unable to provide informed consent
2. Have any medical contraindication to anterior nasal swab (e.g. bleeding disorders, recent facial trauma)

For the costing component we will further conduct exit interviews on 100 purposively selected testers across all use cases.

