#### Recruitment process

Below are the steps to be followed before, during and after screening for eligibility in congregate settings by the study team. Upon notification of a COVID-19 case at any of the selected congregate settings either via PSI or directly or via any other media, the project coordinator will contact the leadership of the institution.

Once confirmed and authorized the study team will then visit the institution within at most a day after being given a go ahead by the leadership of the institution. All available occupants of the congregate institution present at the time will then be screened for eligibility.

Before commencing any data collection, all eligible individuals at the institution will be provided information sheets to read followed by informed consent process completed by a research assistant.

Potential participants who may require more time will be allowed to read information sheets with potential participation on the next day following consent. The project coordinator who is medically trained will be available onsite to answer any clinical questions. Any prospective participant who declines to participate in the study will not be punished and such a decision will not be passed onto any of the institution. Additionally, for prospective participants who decline to participate but show COVID-19 symptoms will be encouraged to be tested through the existing government COVID-19 testing sites.

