### **Recruitment process**

Recruitment process for secondary distribution of self-test kits will begin with a positive COVID-19 test (index). The same research assistant who conducted the initial consenting and baseline data collection for the other use cases will screen the index case for eligibility and complete the written informed consent for the index. All consenting index cases will then be enrolled in the study. Index cases who decline to participate in secondary distribution of self-test kits component of the study will not be disadvantaged in any way and can opt out of the study if no other follow-up activities are due.

Following written, informed consent, index clients will be shown the self-test kits and how to use them and asked to list the fully anonymized details of any household or other close contacts aged 18 years or above. The index will maintain their own contact list using a Paper Enrollment Log (CC03) to assist them with their organization, distribution and documentation of any subsequent steps taken after testing and reporting back to us. If indicated at this stage, written informed consent will also be taken for the costing piece.

At 14 days after recruitment, the data from the enrollment log will be reported back by the index during a telephone interview. The study team will enter this data into simple aggregate format that will be entered electronically as a single aggregate record for each index case (number of contacts; numbers aged over 65 years; numbers offered self-testing; numbers accepting Day 1 self-testing etc.) provided with a) two KN95 masks for themselves; b) a pack of surgical masks to offer to their contacts; and c) two self-test kits to give to each named contact for use immediately and on day 5.

The proportion of contacts linked to care will also be measured and reported. All contacts will be provided with a study leaflet (NC06B) via the index client that explains clearly where to seek care if the self-test result is positive. Additionally, the leaflet provides phone numbers for the project staff who will be on hand to direct positive contacts to the nearest clinic that provides COVID-19 care.

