Outcomes will be collected by telephone interview with the index case two weeks after enrolment. The data from the phone interview will include if the index delivered the COVID-19 self-test kits to the contacts or not, contact used the test kits as advised and if they disclosed the results to index. No personal identifiers will be collected on the contacts, but we will ask the index to identify any known high-risk factors (age over 65 years, or over 50 years with co-morbidity) that would be a potential indication of eligibility for outpatient treatment of the tested contact. If consent has been taken, the participant cost survey will then be administered over the phone as well.

A person shall be considered a contact if they had any one of the following exposures to a confirmed case as suggested by WHO(33):

- face-to-face contact with a confirmed case within 1 meter and for at least 15 minutes;
- direct physical contact with a confirmed case;
- direct care for a patient with probable or confirmed COVID-19 disease without the use of recommended PPE.

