## Outcomes

- i. Cost per kit distributed
- ii. Cost per kit used
- iii. Cost per positive patient diagnosed
- iv. Cost per positive patient diagnosed and linked to prevention and care
- v. Cost per COVID-19 infection and death averted
- vi. Cost of scaling-up COVID-19 self-testing

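### Contacts who already have a current positive diagnosis are not excluded or counted apart, so the yield of secondary distribution can include infections that were found by another route

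*Protocol*

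**What the plan says.** Three groups carry the same exclusion, worded for congregate settings as "Have tested positive for COVID-19 and are still within the isolation period". It appears for health care workers (5.1.1), outpatients (5.1.2) and congregate participants (5.1.3), and again for all three in section 5.3.

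For contacts, the only exclusion list is in section 5.3. It opens "Contacts shall be ineligible for participation if they are" and has two items: inability to consent and a medical reason not to take a nasal swab. Section 5.1.4 adds an age limit and an exposure definition. The index is "asked to list the fully anonymized details of any household or other close contacts aged 18 years or above". Nothing there concerns a contact's current test status.

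The main analysis in 5.1.4 includes the "number of contacts with positive immediate or day 5 results", and a count of contacts diagnosed within five days of symptom onset. Section 5.5 lists "Cost per positive patient diagnosed" among the cost outcomes, and a version for positives linked to prevention and care.

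On data capture, section 5.1.4 states that "No personal identifiers will be collected on the contacts". The log is reported back by telephone in a form "that will be entered electronically as a single aggregate record for each index case". Section 6.2 likewise describes household-level counts.

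**The concern.** The yield of a contact-testing model is useful to policy only if it counts infections that the model found. An already diagnosed contact who uses a kit and tests positive adds to the positive count without adding a diagnosis. The same person enters the denominator of cost per positive, so the model looks cheaper per case than it is.

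The project itself creates some of the overlap. Index cases come from its health care worker, outpatient and congregate components, so colleagues, housemates or household members can be diagnosed by those components and also be listed as contacts. This use case is costed (5.5), and section 2.7 says it will inform whether national contact-tracing policy can change. Yield and cost per positive are figures a ministry would read.

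**Working it through.** **1. The eligibility lists side by side**

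| Group | Tested positive and still isolating is excluded? | Where |
|---|---|---|
| Health care workers | Yes | 5.1.1, 5.3 |
| Outpatients | Yes | 5.1.2, 5.3 |
| Congregate participants | Yes | 5.1.3, 5.3 |
| Index cases | Not applicable, positive by design | 5.1.4, 5.3 |
| Contacts | No | 5.3 |

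The gap is specific to contacts. The rule used elsewhere is narrower than any past positive: it needs a positive test and a current isolation period.

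**2. The plan's own figures**

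- Precision sample at 60% uptake, ±5 points, 95% confidence: 1.96² × 0.60 × 0.40 / 0.05² = 368.8, rounded up to 369. The protocol states 370 (5.1.4) and 369 (5.8). Reproduced.
- Index cases: 30,000 × 2% = 600. Contacts: 600 × (3 + 2) = 3,000. Reproduced.
- Self-testers at 60%: 3,000 × 0.60 = 1,800.

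None of these depends on the contact exclusions.

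**3. Direction for yield**

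Let k be the share of self-testers already diagnosed and p the positivity among the others. If every already diagnosed tester is positive again, counted yield divided by new yield is R = 1 + k / [(1 − k) p]. R exceeds 1 whenever k exceeds 0. Reported cost per positive is the cost per new positive divided by R.

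**4. Size, on assumed values only**

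The documents give neither k nor p. With 1,800 self-testers, each cell shows already diagnosed / new positives, then R:

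| Assumed p | k = 1% | k = 5% | k = 10% |
|---|---|---|---|
| 5% | 18 / 89, 1.20 | 90 / 86, 2.05 | 180 / 81, 3.22 |
| 10% | 18 / 178, 1.10 | 90 / 171, 1.53 | 180 / 162, 2.11 |
| 20% | 18 / 356, 1.05 | 90 / 342, 1.26 | 180 / 324, 1.56 |

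These lie at the upper end for each k, because they assume that every already diagnosed tester is positive again.

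A low anchor comes from section 2.1, which puts the diagnosed share of infections in Africa at 7 per 1,000. Assume 10% of 3,000 contacts are infected (300). Then 300 × 0.007 = 2.1 were already diagnosed. With 60% uptake and the 92.1% sensitivity in section 2.6, 2.1 × 0.60 × 0.921 = 1.2 counted positives, against 297.9 × 0.60 × 0.921 = 164.6 new ones. R = 1 + 2.1 / 297.9 = 1.007. That is a background figure, and the project's own testing would raise the share locally.

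**5. Effect on uptake**

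Here k is the share of listed contacts already diagnosed, and the others accept at 60%.

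- If all of them decline: 0.60 × (1 − k) = 59.4%, 57.0% and 54.0% at k = 1%, 5% and 10%.
- If all of them accept: 0.60 + 0.40k = 60.4%, 62.0% and 64.0%.

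The shift reaches 5 points only at k = 0.05 / 0.60 = 8.3% in the first case, or k = 0.05 / 0.40 = 12.5% in the second.

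**6. Can it be repaired afterwards?**

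With no identifiers and one aggregate row per index case, a listed contact cannot be matched to a health care worker, outpatient, congregate or index record. The fields named in 5.1.4 and 6.2 do not include prior positive status.

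**The case against.** **Yield is not the primary outcome.** The outcome is the proportion of contacts accepting a self-test, the objective is acceptability, and section 5.1.4 calls the analysis exploratory. This stands. The point concerns a secondary count and the cost figures built on it.

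**The overlap may be very small.** Background diagnosis is rare (2.1), national guidance does not require testing of symptomatic contacts (2.6), and 5.1.4 says contact tracing was abandoned. The larger values in the table above restate their assumption: k = 5% with p = 10% means that 90 / 261 = 34% of positive testers already had a diagnosis. Already diagnosed people may also not bother to test, and section 2.1 says sensitivity falls after day 7 of symptoms. All of this stands, and no percentage should be quoted as an estimate.

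**A reader might infer large clusters from outreach.** Section 5.1.3 says "All available occupants of the congregate institution present at the time will then be screened for eligibility", so k people found positive together might seem to generate k(k − 1) positive contacts, or 12 for k = 4. The documents do not support this. That figure counts each of four people three times, which is repeat listing, a different problem. The sentence is about eligibility screening. Research recruitment takes every second eligible person and stops at 323 over at most five settings. At the protocol's 2% positivity that is 323 × 0.02 = 6.5 positives, about 1.3 per setting. Outbreak positivity could be higher, and Table 1 targets 5,000 programme tests, so overlap remains possible. Large mutual clusters are not shown to be typical.

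**The forms or the SAP may deal with it.** CC01, CC02 and CC03 are not shown, the field list in 5.1.4 is open-ended, and section 6.2 records how many adult contacts were eligible. The forms may ask. The protocol does not require them to, and its contact eligibility list would not remove an already diagnosed contact. A SAP can define an analysis set but cannot use an item that was never collected.

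**Conclusion.** The point holds for secondary yield and for cost per positive. The exclusion used in the other three components is missing for contacts, the positive count is not restricted to new diagnoses, and the described data cannot separate the two later. If any already diagnosed contact tests positive again, counted yield is too high and cost per new positive too low.

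The size is unknown. On assumed inputs the inflation factor runs from about 1.01 to 3.2. That width reflects the missing inputs and is not a forecast; a value near the low end is plausible.

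A reader might also infer that the uptake result is compromised or that the sample size is wrong. The documents support neither. The effect on uptake has no fixed direction and is probably within ±5 points, since it would take at least 8.3% of listed contacts already diagnosed, all declining, to exceed that. The 369/370, 600 and 3,000 figures are unaffected.

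**What to change.** Add one count per index case to the index log (CC03) and follow-up form (CC02): how many listed contacts had already tested positive and were still in their isolation period when listed. This matches the rule used for the other three groups.

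Then report that number, report newly diagnosed contacts and cost per new positive without those contacts, and give uptake with and without them. Who is offered a kit does not change.

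The cost is one more item on two existing forms, reported second-hand by the index and so subject to what the index knows, and a slightly smaller contact denominator. If the forms already collect this, only a sentence in the section 5.1.4 analysis is needed.

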**5.4. Qualitative process evaluation**

This data collection activity is an additional activity within each use-case to generate evidence on how best to optimize the delivery of the interventions at scale. A TiDieR (Template for Intervention Description and Replication) summary for each use case will be written up, ensuring that each use-case is reported to the minimum standard to ensure replicability, of interventions. To create the TiDieR framework, semi-structured interviews with the study coordinators will be conducted, complemented by interviews with two implementers on the ground for each use-case (CK01).

Thereafter, the study shall use Proctor's framework (Table 2) for implementation outcomes to evaluate each use-case according to the acceptability, appropriateness, feasibility, and fidelity domains below:

**Table 2. Proctors' implementation outcomes**

| Implementation outcome | Level of analysis                                                  | Available measurement                                                                                                                                                 |
|------------------------|--------------------------------------------------------------------|-----------------------------------------------------------------------------------------------------------------------------------------------------------------------|
| Acceptability          | Participants across all use cases
+ 2 implementers per use case | Semi-structured interviews                                                                                                                                            |
| Adoption (uptake)      | PSI programme                                                      | Programme data for each use case: 
 
• Number tested
 
• Number linked to care
 
• Number receiving care
 
 |
| Appropriateness        | Participants across all use cases
+ 2 implementers per use case | Semi-structured interviews                                                                                                                                            |
| Costs                  | Costing data across all use cases                                  | Costing and cost effectiveness study
Health system, user costs and societal downstream costs.                                                                      |
| Feasibility            | Participants across all use cases
+ 2 implementers per use case | Semi-structured interviews                                                                                                                                            |
| Fidelity               | Participants across all use cases
+ 2 implementers per use case | Semi-structured interviews                                                                                                                                            |
| Penetration            | PSI programme                                                      | Scaled to other programme sites                                                                                                                                       |

The participant sampling strategy for each semi-structured interview will follow the framework in Table 3 below:

